## Abstract

**Background:**

Neonatal mortality remains high in many low- and middle-income countries (LMICs), with neonatal sepsis and antimicrobial resistance (AMR) posing significant threats to newborns, particularly in sub-Saharan Africa (SSA). Tanzania is among the countries with the highest neonatal mortality rates, with sepsis being a major contributor.

Gut dysbiosis has been identified as a risk factor for neonatal sepsis in high-income countries, due to factors like abundance of pathogenic bacteria, decrease in microbiome diversity, intestinal barrier defects and bacterial translocation. Understanding gut dysbiosis in the local setting and its role in sepsis development may offer new prevention strategies, such as probiotics for high-risk preterm infants.

**Objectives:**

This prospective neonatal cohort, established at Muhimbili National Hospital (MNH) in Dar es Salaam, Tanzania, aims to analyze the gut microbiome of preterm infants and explore associations with neonatal late-onset sepsis (LOS). Additionally, data on bacterial pathogens of bloodstream infections and AMR prevalence will be identified. Secondary endpoints include clinical LOS, sepsis-related death, death from any cause, and hospital discharge outcomes.

**Methods:**

Eligible preterm neonates (28 + 0 to <34 weeks of gestational age, birth weight ≥ 1000g) will be recruited with maternal consent. Socio-demographic and clinical data, microbiological details of blood pathogens, and a set of fresh frozen fecal samples during the 28 days observation period will be collected. The study targets a sample size of 1350 participants and we expect 72–135 culture-proven LOS during a study period of 18 months. Fecal samples will undergo next-generation sequencing (NGS) to analyze microbial community functions in comparison to matched controls.

**Discussion:**

This collaborative study between universities in Tanzania and Germany, aims to analyze the neonatal microbiome in relation to sepsis development and AMR of blood culture isolates to enhance neonatal sepsis care, improve diagnostics and treatment. The project will offer insights into potential therapeutic strategies for the future, promote academic exchange, capacity building and research on African microbiomes.

## Introduction

Despite significant progress in reducing child mortality, neonatal mortality remains alarmingly high in many low-and middle-income countries (LMICs). One of the major global contributors to neonatal mortality is sepsis [1], which is further complicated by the increasing antimicrobial resistance (AMR) of pathogens [2,3]. It is vital to understand the epidemiology of neonatal sepsis and AMR at local, regional, and national levels in LMICs to develop effective treatment and prevention strategies.

Tanzania is among the countries with the highest newborn mortality in sub-Saharan Africa (SSA), with sepsis being one of the major causes of death [4]. The Tanzanian government, through the Ministry of Health, launched a strategic plan to accelerate the reduction of maternal and newborn deaths and is currently working to establish well-equipped and properly staffed neonatal units in all regional referral and district hospitals [5,6]. The need assessment for this project was based on opinions from international experts, as well as results from local studies done on neonatal sepsis [7–10].

Recent advances in neonatal care services, the establishment and improvements in neonatal care units (NCU) in Tanzania have seen even more preterm and very low birth weight (VLBW) neonates surviving the first weeks of life. However, VLBW neonates also have the highest risk for late-onset sepsis (LOS) and necrotizing enterocolitis (NEC) with high morbidity and mortality and serious short and long-term health consequences [8]. A recent multicenter global study conducted in LMICs reported that 21% of VLBW neonates experience at least one episode of blood culture-proven LOS [10]. Various factors are associated with intestinal inflammation and bacterial translocation into the bloodstream, including their intestinal barrier immaturity, their premature immune system, and gut microbiota dysbiosis [11].

In resource-limited clinical settings, identification of pathogens causing neonatal sepsis and analysing AMR profiles remain challenging. Isolated bacteria are increasingly resistant to first and second-line antibiotics recommended by the WHO [12,13]. Extended-spectrum beta-lactamases (ESBL)-positive *Klebsiella* and *E. coli* spp. are reported to become the most common causes of neonatal sepsis in SSA with rapid emergence of carbapenem-resistant *Enterobacterales* [14]. New and affordable antibiotics for the treatment of multi-drug resistant (MDR) neonatal sepsis are lacking [15], therefore, in addition to the development of new drugs, infection prevention control (IPC) is pivotal.

Establishing reliable sepsis and AMR diagnostics through blood cultures of neonates admitted to NCUs is crucial for identifying bloodstream infections and determining antimicrobial susceptibility, allowing clinicians to prescribe antibiotics more efficiently and appropriately. A large multi-country study, including our study site, published by NEST360 in 2023, highlighted a significant gap: while 70% of neonates were prescribed antibiotics, only 6% had blood cultures taken, missing critical opportunities for infection detection [16]. The authors concluded that there is an urgent need to improve diagnostics, and develop individualized strategies for the prevention and treatment of LOS in LMICs.

The peak incidence of LOS occurs between the second and third week of life [17] after being exposed to various factors in the NCU environment and exposures to various invasive procedures and antibiotics altering the neonatal microbiome [18]. The hypothesis of gut dysbiosis preceding the development of LOS and NEC in preterm babies has been developed, based on findings of alterations in their gut microbiome in terms of specific metabolites and reduced biodiversity before disease onset [19–21]. Importantly, several conventional culture studies have demonstrated concordance between isolates cultured in blood and bacteria residing in the infants’ gut [22,23].

Recent advances in molecular microbiology and bioinformatics including next-generation sequencing have enabled direct and deep sequencing of bacterial DNA from stool samples of neonates to describe the gut microbiome, identify dysbiosis, and investigate its impact on the risk of developing sepsis and AMR transmission. The aim of this study is to analyze maternal and neonatal gut microbiome and the risk to develop LOS or NEC. This collaborative academic partnership study is, to our best knowledge, the first to examine the gut microbiome of preterms in Tanzania.

### Research questions

Our primary research question aims to answer whether gut dysbiosis precedes the development of LOS and/or NEC in Tanzanian preterm neonates and whether microbial or metabolomic markers predict neonates at high risk. Secondary research questions include 1) What are the maternal and neonatal risk factors for LOS and/or NEC? 2) What are factors associated with disease severity and outcomes? 3) What bacteria species and AMR profiles are found in blood culture isolates of preterm neonates with LOS and/or NEC?

## Materials and methods

### Study design

This study will be a case-control study nested into a hospital-based, single-center, observational neonatal cohort. Recruited preterm neonates will be followed over their first 28 days of life. The primary clinical endpoint in this study is a blood culture (BC)-proven LOS. Secondary endpoints are clinical sepsis, NEC, death to clinical and/or BC-proven sepsis or NEC, death to any cause, or discharge from the hospital with or without sequelae.

### Study setting

The study will be conducted at the Muhimbili National Hospital (MNH) in Dar es Salaam, the business and commercial center of Tanzania. MNH is the country’s largest and highest referral care center receiving newborns throughout the country, specifically from all regional referral sites. MNH is the teaching hospital for the Muhimbili University of Health and Allied Sciences (MUHAS) and other medical universities.

The Neonatal Care Unit (NCU), located near the obstetric theater and maternal wards, includes the preterm unit (Ward 37), term unit (Ward 36), and Kangaroo Mother Care (KMC) unit, with a total capacity of 137 beds, including 14 NICU beds equipped with 10 mechanical ventilators. The High Dependency Unit (HDU) accommodates 10 neonates in warmer beds with CPAP support. Over the past four years, the unit has been upgraded to a level III NICU – one of only four in the public sector in the entire country – through significant investments in infrastructure, equipment, and staff training. The introduction of the Master of Science in Clinical Neonatology program in 2021 has further enhanced preterm care standards by training pediatricians as specialized neonatologists.

The NICU and HDU beds usually serve as stations for the sick preterm admissions before transitioning to Ward 37 for completion of treatment or further observation, after which they are either discharged home or referred to the close-by KMC unit for weight monitoring and feeding progression. The discharge criteria for preterm neonates include reaching a minimum weight of 1.5 kg, consistent weight gain of 15–30 g/kg/day, being in stable health, and receiving full enteral feeds either by cup or breastfeeding. After discharge, preterm infants are routinely followed up weekly at the outpatient neonatal clinic until they reach a weight of 2.5 kg. The NCU receives approximately 4000 neonatal admissions per year. Specifically, around half of these (150–180 admissions per month) include prematurely born babies with gestational age (GA) of less than 34 weeks.

### Study population and sample size

The study participants will include inborn and outborn preterm neonates born at 28 + 0 to <34 weeks of GA admitted to the neonatal wards, and their respective mothers who consented to participate after a detailed description of the study has been given by trained study team members. Recruited preterm neonates should have a minimal weight of at least 1000 g and be enrolled within their first week of life. We will exclude infants whose mothers are below 18 years of age, have severe, life-threatening illness at the time of admission, and/or have severe comorbidities or severe congenital malformations. Furthermore, neonates or mothers who ever received probiotic supplements during pregnancy will be excluded from this study.

Sample size calculations considered all study objectives and the one requiring the largest sample size will be the basis to determine recruitment numbers. All eligible preterm neonates admitted to the neonatal unit during the 18-month study period will be recruited and closely followed up for 28 days each.

To answer the primary research question on the hypothesis of preterm neonates developing gut dysbiosis before the onset of sepsis we need to identify preterms with BC-proven sepsis, assess their microbiomes, and compare it with controls (matched for GA, sex, mode of delivery, type of feeding, and previous antibiotic exposure). Assuming a rate of BC-proven sepsis of 10% and 25% missed samples we expect to identify 72–135 bloodstream pathogens (positive BCs) with 54–101 complete sets of stool samples for microbiome analysis within 18 months [7,10]. According to Graspeuntner *et al.,* we then expect gut dysbiosis in 30% of the neonates without and 60% of the children with LOS [19].

Our minimal sample size considerations are based on the proportions of gut dysbiosis in children with and without LOS. Assuming an alpha level of 5% and a power of 80% a minimal study number of 84 children (42 with and 42 without LOS) is needed to reject the null hypothesis that no difference in the proportion of dysbiosis between both cases and controls. Cases are defined as preterm neonates who develop LOS and controls as preterm neonates who do not develop any clinical or culture proven sepsis during the observation period (after 72 hours of life).

The calculations are based on formulae 1 for a two-sample proportions test, where *n*_*i*_ is the sample size estimated for each group, z is the normal deviation defined for the alpha level (α) and the study power (β), and *p*_*i*_ is the proportions in the respective groups.

$$n_{i}=\frac{{\left(Z\alpha /2+Z1-\beta \right)}^{2}*(p1(1-p1))+(p2(1-p2))}{{\left(p1-p2\right)}^{2}}$$
(formulae 1)

These parameters define minimal study numbers to reach power and significance. We aim to include all cases of LOS and NEC with complete microbiome and a higher number of controls, to improve the statistical power of the study, precision of the applied data analysis and allow potential subgroup analyses [19].

In the literature, the rate of positive BCs varies between study sites and is highly dependent on the quality of diagnostic procedures as well as the amount of blood transferred into BC bottles. Based on the available data and our experiences we are expecting to screen 80–100 admissions per month in the respective GA range and a study inclusion rate of 50–75%. Thus, we expect to recruit approximately 40–75 admitted newborns per month for a period of 18 months, which amounts to 720–1350 admissions over the study period. The calculations were enforced by comparing data from previous studies [7,24] and the ongoing NEST360 survey in the NCU [25], powered to identify sepsis incidence, risk factors, and mortality rates of LOS and NEC among preterm neonates.

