### Variables to predict LOS and gut dysbiosis

Variables have been selected based on a literature search and local clinical experience. Table 1 shows factors predicting LOS and gut dysbiosis that will be captured during the study period. Independent variables will be categorized as socio-economic, neonatal, maternal, and septic risk factors (Table 1).

**Table 1 pone.0325099.t001:** Candidate variables for predicting LOS and gut dysbiosis.

Socio-economic factors	Neonatal factors	Maternal factors	Septic risk factors
Maternal education level	Gestational age	Age at delivery	Invasive ventilation
Self-rated household income	Sex	Parity	Central line at least 48 hrs
Family health insurance	Birth weight	Previous stillbirths	Parenteral nutrition
	Multiple births	HIV status	Presence of any maternal risk factors
	APGAR score at 1 minute	Medical conditions	Type of feeding
	APGAR score at 5 minutes	Pregnancy complications	
	Place of birth	Maternal antibiotic exposure 3 months before delivery	
	Delivery complications		
	Antibiotic exposure and type		
	Type of delivery		

During the observational period of 28 days clinical signs and symptoms of LOS and/or NEC, BC results with phenotypic identification, and antibiotic susceptibility testing, the previous use and type of antibiotics, and the clinical outcomes, will be recorded by the study team in electronic data capture forms. Stool samples for microbiome analysis will be collected in a standardized manner on day 1–3, and days 7, 14, 21 (each ±3) and neonates’ type of feeding in the last 24 hours will be categorized as exclusive human milk (no formula given), breastfed mainly (>80% feeds breastmilk/human milk), formula feed (>50% of feeds include formula), only formula (no human milk), or no enteral feeding at all.

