### Statistical analysis

Descriptive statistics will be used to summarize the demographic and clinical characteristics of the study population, including gestational age, birth weight, gender, mode of delivery, and presence of comorbidities. Mean and standard deviation or median and interquartile range for continuous variables will be used and for categorical data frequencies or proportions will be described.

To answer the first objective on the incidence and risk factors of LOS, the incidence density will be calculated as the number of new cases of LOS divided by the total person-time at risk in the cohort. The person-time at risk will be calculated by summing the individual follow-up durations until the occurrence of BC-proven LOS (clinical sepsis, NEC, and death).

Cox-proportional hazard regression will be utilized to investigate the relationship between the risk factors and risk to develop primary and secondary endpoints. First, we will perform univariate cox-regressions for potential risk factors to identify individual risk factors, all variables considered relevant for the study question will be included in the multivariate cox-regression to adjusting for potential confounders. The hazard ratios (HRs) with the 95% confidence intervals (CIs) will be estimated for each risk factor. Etiological agents of LOS/NEC and the respective AMR patterns will be described as the proportion of isolates resistant to each antibiotic and according to international standard.

Microbiome analysis will be performed to evaluate gut dysbiosis in preterm infants prior to the development of LOS and in relation to the microbiome of the mother. Association of relative abundances of microbial species with the factors of gestational age, days of life, diet, and LOS will be limited to species that were found with a non-zero relative abundance in at least 40 stool metagenomes. Square root-transformed relative abundancies will be used and analysed using linear mixed effect (LME) models, where repeatedly collected microbiome data from each child is considered to cluster.

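### Place of birth, a listed candidate predictor of both LOS and gut dysbiosis, is neither a matching factor nor a named term in the microbiome model, so the dysbiosis-LOS association could be confounded by inborn/outborn status

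*Protocol article*

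**What the plan says.** - **Who is enrolled** (Study population and sample size): both birth groups enter one cohort. The plan states: "The study participants will include inborn and outborn preterm neonates born at 28 + 0 to <34 weeks of GA". Infants must "be enrolled within their first week of life".
- **Where they come from** (Study setting): the hospital is the country's "highest referral care center receiving newborns throughout the country, specifically from all regional referral sites".
- **Matching** (Study population and sample size): the cases' microbiomes are assessed in order to "compare it with controls (matched for GA, sex, mode of delivery, type of feeding, and previous antibiotic exposure").
- **Microbiome model** (Statistical analysis): relative abundances of species are related by linear mixed models "with the factors of gestational age, days of life, diet, and LOS", with clustering by child.
- **What is recorded** (Variables to predict LOS and gut dysbiosis): Table 1, titled "Candidate variables for predicting LOS and gut dysbiosis", includes "Place of birth" among the neonatal factors.
- **Adjustment elsewhere** (Statistical analysis): the multivariable Cox regression is open to any variable judged relevant. It models clinical endpoints and is not the microbiome comparison.

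**The concern.** A variable confounds the dysbiosis-LOS comparison if it is related to early gut flora and also affects LOS risk by a route other than that flora. The protocol treats place of birth as a candidate predictor of both. Birthplace also precedes both the flora and the LOS episode, so adjusting for it does not remove part of a pathway from flora to sepsis.

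The plan names two steps that could control it: the choice of controls and the terms of the mixed model. Neither includes it. Gestational age, sex, mode of delivery, feeding and antibiotic exposure may carry some of the difference between inborn and outborn infants, but none records where the infant was first colonised. Days of life does not record it either.

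At stake is the reading of the primary result. Flora acquired at a referring site could appear as flora that precedes LOS. Recruiting more cases or controls would not remove this; it would make a spurious difference easier to declare significant.

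**Working it through.** **1. The plan's own figure.** The stated minimum is 42 per group, from dysbiosis of 30% without and 60% with LOS, two-sided alpha 5% and power 80%. With pooled variance and a mean proportion of 0.45:

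n = [1.960 × √(2 × 0.45 × 0.55) + 0.842 × √(0.30 × 0.70 + 0.60 × 0.40)]² / 0.30² = (1.379 + 0.565)² / 0.09 ≈ 42.

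The figure reproduces and is not in dispute. It assumes that the two groups differ only through LOS.

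**2. The lists side by side.**

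| Variable | Matching | Mixed model | Table 1 |
|---|---|---|---|
| Gestational age | yes | yes | yes |
| Sex | yes | no | yes |
| Mode of delivery | yes | no | yes |
| Feeding / diet | yes | yes | yes |
| Antibiotic exposure | yes | no | yes |
| Days of life | no | yes | no |
| Place of birth | no | no | yes |

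**3. How large could it be?** The documents give no outborn share, no LOS risk by birthplace and no flora by birthplace. All of the following inputs are assumptions. Within inborn and within outborn infants, LOS and flora are taken as unrelated, so the true odds ratio (OR) is 1. Controls are taken simply as infants without LOS.

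Let q be the outborn share, and let Lo and Li be the LOS risks of outborn and inborn infants.

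- Outborn share of cases = q·Lo / [q·Lo + (1 − q)·Li]
- Outborn share of controls = q·(1 − Lo) / [q·(1 − Lo) + (1 − q)·(1 − Li)]
- Proportion with the flora feature = inborn rate + outborn share × (outborn rate − inborn rate)

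Central case: q = 30%, LOS 16% against 8%.

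- Overall LOS: 0.30 × 0.16 + 0.70 × 0.08 = 10.4%, close to the plan's 10%.
- Outborn share of cases: 0.048 / 0.104 = 46.2%. Of controls: 0.252 / 0.896 = 28.1%.
- Dysbiosis 60% outborn, 30% inborn: cases 0.30 + 0.462 × 0.30 = 43.8%; controls 0.30 + 0.281 × 0.30 = 38.4%; OR 1.25. A two-sided 5% test rejects about 8%, 9% and 12% of the time at 42, 54 and 101 per group.
- Carriage of one species 40% outborn, 5% inborn: cases 0.05 + 0.462 × 0.35 = 21.2%; controls 0.05 + 0.281 × 0.35 = 14.8%; OR 1.54. Rejection is about 12% at 42 per group. With 101 cases and 202 controls (the 1:2 ratio is also assumed) it is 26-29%, depending on whether the variance is unpooled or pooled.

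Range over q = 20-50%, outborn LOS 12-20% and inborn LOS 8%:

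- Lowest, for dysbiosis, at q = 20% and LOS 12% against 8%: outborn share 0.024 / 0.088 = 27.3% of cases and 0.176 / 0.912 = 19.3% of controls; dysbiosis 38.2% against 35.8%; OR 1.11.
- Highest, for species carriage, at q = 20% and LOS 20% against 8%: outborn share 0.040 / 0.104 = 38.5% of cases and 0.160 / 0.896 = 17.9% of controls; carriage 18.5% against 11.3%; OR 1.79.

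A more extreme assumption goes higher: outborn infants set directly at 70% of cases and 30% of controls, with dysbiosis 60% against 20%, gives 48% against 32%, OR 1.96.

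**4. When it vanishes.** If LOS risk is the same in both groups, the outborn shares of cases and controls are equal and the OR is 1.00. If the flora does not differ by birthplace, the OR is also 1.00.

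**The case against.** Several objections carry weight.

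- **Place of birth is one of many.** Table 1 has 25 entries, and matching and model together cover five. Birth weight, multiple births, ventilation and central lines are among the 20 left out, and no design can match on all of them. This stands. Place of birth merits a term because the exposure is gut flora and the site draws transfers from the whole country, but the documents do not rank it above the rest.
- **The covariate list may not be closed.** The article condenses a fuller plan, and it does not say that the named model factors are exhaustive. This also stands in part. The point rests on two lists that are stated without the variable, while open adjustment is written only for the Cox models.
- **The illustration is not the planned analysis.** It uses unmatched groups and a binary feature; the plan uses matched controls and mixed models on transformed abundances. Matching on feeding and antibiotics may remove part of the imbalance. This is right, and it is why the figures show only a possible size.

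A reader might also infer more than the documents support:

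- *That Table 1 states an effect of birthplace on both outcomes.* Its title says candidate variables, and the heading covers the table as a whole.
- *That outborn infants spend their first days elsewhere.* The first-week limit concerns enrolment; the time of transfer is not given. Requiring complete stool sets, with a first sample on day 1-3, would tend to limit late arrivals.
- *That a confounded species has no predictive value.* The research question also asks which markers predict high risk. A species with a marginal OR of 1.54 would still predict LOS, though not causally.

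**Conclusion.** The point holds as a possibility of confounding that the plan can guard against cheaply. The text confirms that inborn and outborn infants are pooled, that place of birth is listed as a candidate predictor of both LOS and dysbiosis, and that it is in neither the matching list nor the named model terms.

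The size is unknown. Under the assumptions shown, the spurious OR is about 1.1 to 1.8, with rejection rates from near nominal to several times 5%. It is 1 if outborn infants have the same LOS risk, or the same flora, as inborn infants. A conclusion that the primary comparison is biased would need evidence of both differences, and the documents report neither. The concern applies to the aetiological reading, that dysbiosis precedes and contributes to LOS. It applies less to pure prediction.

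**What to change.** 1. Add inborn/outborn status as a fixed effect in the species-level mixed model, and report the LOS coefficient with that term included.
2. Add the same term as an adjustment in the case-control comparison of the dysbiosis proportion.
3. Report an inborn-only sensitivity analysis, and tabulate inborn/outborn status for cases and controls so that readers can see whether the groups differ.

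No new data are needed if the recorded place of birth distinguishes inborn from outborn, as it is read here. The cost is about one degree of freedom and slightly wider intervals; the inborn-only analysis will be less precise.

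Two further steps are optional. Exact matching on inborn/outborn status would balance the factor by design but may leave some cases without a control. Days since admission to the neonatal unit could be added, but in inborn infants it is nearly collinear with days of life, so it would be informed almost entirely by the outborn group.
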